### Data Management and Analysis

Data will be collected on tablet that will be password protected and uploaded to a secure password protected server. No names will be collected on assessment materials (all deidentified). Sessions will be audio recorded on secure devices and delete once they are uploaded to the secure drive. Written materials such as consent and assent forms will be stored in a locked drawer in a locked office (See confidentiality for more details).

**Analysis.** (Aim 1) Quantitative longitudinal analysis will explore changes in depression and secondary outcomes from baseline to 3-month post-treatment based on intention-to-treat. Descriptive measures will be used to summarize data. Depression changes between baseline and post, 1-month post, and 3-month follow-up will be compared in the LEAD versus WL arms through mixed-effects linear regression models, with fixed effects for study condition, time, and the interaction between condition and time.

(Aim 2) Mixed-methods: quantitative and qualitative findings will be equally valued, analyzed separately, then integrated guided by hypothesized change pathways. **Quantitative:** we will explore pathways using structural equation modeling with data from Baseline, During Treatment [proximal mechanisms], Post, 1-month, and 3-month post. We will conduct a path analysis. We will explore 3 pathways: (1) the indirect effect of LEAD on father; (2) the direct and indirect effect of father depression on child MH via parenting, and (3) if we detect relationships in path 1 and 2, we will explore the direct and indirect effects of LEAD on child MH via father's depression. **Qualitative:** We will use the Framework Method with inductive and deductive coding. Two RAs will familiarize themselves with interview and session

transcripts. Next, they will open-code transcripts line-by-line, then deductively code transcripts. Once data are

coded, they will be charted and assessed with a framework matrix. Results will clarify and contextualize mechanisms, and potential moderators, to test in a future trial. (Aim 3) Table 3 shows measures for Aim 3.

Interviews and focus groups will be analyzed using the Framework Method. **Participation** will be analyzed as % of eligible fathers who enroll in LEAD and % excluded; *retention* will be % of fathers attending  $\geq 1$  session, attending  $\geq 75\%$  of sessions, and dropping out. We will explore retention rates across both arms. To examine **fidelity** and **counselor competency**, all sessions will be audio recorded; 25% will be transcribed, translated to English, and reviewed by the PI and the PC. We will conduct consensus ratings on the first 4 transcripts, then reach 80% agreement on ratings before independently rating the remainder. Fidelity will yield two scores: (1) % of steps completed based on proportion of

| Table 3. Aim 3 Assessment of Implementation Outcomes        |                 |                       |
|-------------------------------------------------------------|-----------------|-----------------------|
| Measure                                                     | Reporter        | RE-AIM Domain         |
| Acceptability                                        |                 |                       |
| Semi-structured interview                                   | F               | Adoption       |
| Focus Groups                                                | PF, S, CL, H    |                       |
| Acceptability of Intervention Measure (4-item Survey)       | PF, S, CL, H, F |                       |
| Intervention Appropriateness Measures (4-item survey)       | PF, S, CL, H, F |                       |
| Feasibility                                          |                 |                       |
| Father participation: % enrolled & % excluded               | Tracked         | Reach          |
| Fidelity Checklist: Adherence & Delivery Quality | Coded           | Implementation |
| Counselor Competency (ENACT Scale)                          | Coded           |                       |
| Retention: Attendance & Attrition                           | Tracked         |                       |
| Semi-structured interview                                   | F               |                       |
| Focus Groups                                                | PF, S, CL, H    |                       |
| Feasibility of Intervention Measure (4-itme survey)         | PF, S, CL, H, F |                       |

PF=Peer-father counselor; S=Supervisor; F=Father; CL=community leaders; H= Hospital Staff; RA's complete assessments; **Effectiveness Aim 1, 2 focus.**

LEAD components delivered as intended and (2) mean quality scores across steps for each case.

**Counselor competency** will be calculated as score averages per counselor session.

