### Specific Aims

**Aim 1. Explore the preliminary effectiveness of LEAD on father MH.** The *primary outcome* is father depressive symptoms assessed by the Patient Health Questionnaire, previously validated in Kenya. *Secondary outcomes* include fathers' drinking, father parenting, interparental problems, and child MH (ages 8-17) reported by the father, co-caregiver, and one child immediately and 1-month and 3-months post-LEAD.

**Aim 2. Use mixed methods to explore mechanisms driving change in father MH, father parenting, and child MH.** I will use structural equation modeling to explore clinical mediators between LEAD and father and child MH: LEAD → positive activities → father MH → parenting → child MH. To explore patterns of response/non-response, I will conduct qualitative interviews (fathers, co-caregivers, children, peer-counselors) on perceived change pathways and analyze LEAD-session transcripts of families showing different change outcomes (e.g., all changed, none, father MH only, child MH only). Qualitative data will be analyzed using the Framework Method. Data will be integrated to generate hypotheses and refinements.

**Aim 3. Explore feasibility and acceptability of implementing task-shifted MH treatment for fathers.** A mixed-methods process evaluation with fathers, peer-fathers, and delivery stakeholders will explore *implementation outcomes*: reach; retention; fidelity; feasibility; acceptability; and barriers to/facilitators of implementation, scale-up, and sustainability, including questions related to social determinants of health, e.g., gender norms, poverty, (interviews, focus groups, surveys).

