## Data Collection and Sampling and Power

We will compare LEAD to a monitored waitlist control (WL) on preliminary clinical and implementation outcomes. Using a random number generator in RStudio, we will randomize participants 2:1 to LEAD:WL, stratified by levels of drinking to ensure group exchangeability. Assessments will occur at baseline, immediately following LEAD, 1-month, and 3-month post-intervention. WL participants will be assessed at each timepoint; after the last assessment (~4.5 months), they will be offered LEAD.

Each father and his co-caregiver and designated child will complete assessments on family problems and MH at each timepoint (both arms); a procedure previously piloted. For fathers in LEAD, proximal mechanism outcomes will be assessed during LEAD (e.g., activity completion; Table 2). A subset of fathers, co-caregivers, and children in the LEAD arm will complete qualitative interviews 1 month after LEAD; peer-father counselors (N=12) and delivery stakeholders (supervisors, community leaders, MTRH personnel) will complete focus group

discussions and  
brief surveys 1-  
month post-LEAD.  
Trained Kenyan RAs  
will conduct  
assessments in

| Table 2. Aim 1 and Aim 2 Quantitative Measures |                                     |                                         |          |     |                     |
|------------------------------------------------|-------------------------------------|-----------------------------------------|----------|-----|---------------------|
| Outcome                                        | Construct                           | Measures*                               | Reporter | Aim | Alpha in Kenya      |
| Primary                                        | Depression Symptoms                 | PHQ-9                      | F        | 1   | .91                 |
| Secondary                                      | Drinking; Gender Norms              | AUDIT  ; GEM  | F        | 1   | .89; .56            |
|                                                | Disrupted Parenting +    | APQ                     | F, Co, C | 1   | F=.78, P=.85, C=.92 |
|                                                | Interparental Problems + | Togetherness Scale         | F, Co, C | 1   | F=.95, P=.96, C=.95 |

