|                                                | Child Mental Health                 | SDQ                     | F, Co, C | 1   | F=.75, P=.75, C=.75 |
| Proximal Mechanism                             | Treatment Engagement                | Attendance                              | Tracked  | 2   | (% attended)        |
|                                                | Activity Completion +    | Homework Completion                     | PF, T    | 2   | (% complete)        |

|                                                                   |            |                                   |                          |       |   |                    |
|-------------------------------------------------------------------|------------|-----------------------------------|--------------------------|-------|---|--------------------|
| Swahili (with translation to English as needed) on secure tablets |            | Positive Reinforcement*           | Activity Emotion Valence | PF, T | 2 | (% + or -; yes/no) |
|                                                                   | Covariates | Age, Religion, Number of children |                          |       |   |                    |

**Notes:** F=father; Co=co-caregiver; C=child; PF=peer-father counselor; T=tracked; PHQ=Patient Health Questionnaire; AUDIT=Alcohol Use Disorder Identification Test; GEM=Gender-Equitable Men; APQ=Alabama Parenting Questionnaire; SDQ=Strengths & Difficulties Questionnaire; \*= Each measure transculturally translated, adapted, and tested in Kenya. += As per Figure 5, path 1 and 2 hypothesized mechanisms

with on-call access to a project psychologist/psychiatrist. Assessors will be blinded to condition.

Assessments will be conducted verbally unless a participant prefers otherwise. Participants will be compensated for travel and time.

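### The Aim 1 model leaves baseline PHQ-9 free to differ by arm, so it compares change scores and gives up precision that a common baseline mean or baseline adjustment would keep

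*Protocol*

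**What the plan says.** The protocol, Data Management and Analysis (Aim 1), sets both the contrast and the model. The contrast is stated as "Depression changes between baseline and post, 1-month post, and 3-month follow-up will be compared in the LEAD versus WL arms". The model is a linear mixed model "with fixed effects for study condition, time, and the interaction between condition and time". No other term is listed there.

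Data Collection and Sampling and Power gives the visit schedule ("Assessments will occur at baseline, immediately following LEAD, 1-month, and 3-month post-intervention") and the allocation: "we will randomize participants 2:1 to LEAD:WL, stratified by levels of drinking to ensure group exchangeability". Table 2 in that section names three covariates ("Age, Religion, Number of children"). It does not tie them to the Aim 1 model, and neither baseline PHQ-9 nor the drinking stratum is among them.

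Nowhere does the protocol constrain the two arms to one baseline mean, adjust for baseline PHQ-9, or put the stratum in the model.

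**The concern.** Randomisation makes the expected baseline PHQ-9 equal in the two arms. A model with a free condition effect at baseline ignores this. It estimates a separate baseline mean for each arm and subtracts the whole of any chance difference from the follow-up difference. That is the right correction only if follow-up PHQ-9 moves one-for-one with baseline, and the slope is usually below 1.

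With 60 and 30 fathers the baseline difference has a standard error of √(1/60 + 1/30) = 0.22 SD, so chance imbalances of up to about 0.44 SD are ordinary. Subtracting them in full adds noise to the estimate.

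What is at stake is the precision of the primary contrast in a small trial whose estimates are meant to inform a definitive one. Separately, the design stratifies on drinking while the stated analysis leaves that factor out.

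**Working it through.** **Inputs from the protocol.** Analysed fathers: 60 LEAD and 30 waitlist (Power paragraph). Four visits. PHQ-9 entry window: above 5 and not above 19 (Table 1). No PHQ-9 SD and no baseline-to-follow-up correlation is given.

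**Assumptions.** Correlation ρ = 0.3, 0.5 or 0.7. Follow-up SD = 1. Baseline SD = k times the follow-up SD, with k = 1, 0.8 or 0.6. Complete data, time as a category, the same ρ between all visits.

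**The plan's own figure.** The protocol states no precision for this contrast, only 80% power from an effect size of 0.60 upward. For 60 and 30, two-sided z-test, alpha 0.05: 0.60/√0.05 = 2.683, less 1.960 = 0.723, which gives 76.5%. The effect detectable at 80% power is 2.80 × 0.2236 = 0.626. That shortfall is a separate matter, and nothing below depends on it.

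**Step 1: the stated model.** With a free baseline mean per arm, the condition-by-time term is the difference in mean change. Per-father variance = k² + 1 − 2ρk, which is 2(1 − ρ) when k = 1.

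**Step 2: common baseline mean, or baseline as covariate.** Per-father variance = 1 − ρ².

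**Step 3: the difference.** (k² + 1 − 2ρk) − (1 − ρ²) = (k − ρ)², which cannot be negative. Handling baseline therefore never costs precision, apart from a degree of freedom or so.

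**Step 4: equal SDs (k = 1).** SE = √(per-father variance × 0.05), since 1/60 + 1/30 = 0.05.

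| ρ | SE, free baseline | SE, common baseline | Variance ratio | SE reduction | 90 fathers are worth |
|---|---|---|---|---|---|
| 0.3 | √(1.40 × 0.05) = 0.265 | √(0.91 × 0.05) = 0.213 | 0.65 | 19% | 90/0.65 ≈ 138 |
| 0.5 | √(1.00 × 0.05) = 0.224 | √(0.75 × 0.05) = 0.194 | 0.75 | 13% | 90/0.75 = 120 |
| 0.7 | √(0.60 × 0.05) = 0.173 | √(0.51 × 0.05) = 0.160 | 0.85 | 8% | 90/0.85 ≈ 106 |

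An exact generalised least squares calculation for the full four-visit model gives the same standard errors.

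**Step 5: baseline SD narrowed by the entry window.**

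| k | ρ | Variance ratio | SE reduction |
|---|---|---|---|
| 0.8 | 0.3 | 0.91/1.16 = 0.784 | 11% |
| 0.8 | 0.5 | 0.75/0.84 = 0.893 | 6% |
| 0.8 | 0.7 | 0.51/0.52 = 0.981 | 1% |
| 0.6 | 0.3 | 0.91/1.00 = 0.910 | 5% |
| 0.6 | 0.5 | 0.75/0.76 = 0.987 | 1% |
| 0.6 | 0.7 | 0.51/0.52 = 0.981 | 1% |

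**Step 6: the drinking stratum.** Let it explain a share q of PHQ-9 variance, equally at every visit (q = 5% or 10%, assumed).

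- In the stated model a constant stratum effect cancels within each father's change. The SE stays at 0.265, 0.224 and 0.173 with or without the stratum.
- Once baseline is handled, the per-father variance with the stratum is (1 − q) − (ρ − q)²/(1 − q), against 1 − ρ² without it. At ρ = 0.3 this is 0.884 (q = 5%) or 0.856 (q = 10%) against 0.910, so omission adds 1.4% or 3.1% to the SE. At ρ = 0.5 it adds 0.9% or 1.9%; at ρ = 0.7, 0.5% or 1.0%.

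**The case against.** The strongest reply has three parts. The stated model is a standard longitudinal analysis and is unbiased under randomisation. Aim 1 is exploratory, in a pilot that says it is not powered for definitive effects. And baseline constraints and stratum terms are often settled in a statistical analysis plan, which is not at hand. The first two stand and limit the weight of the point. The third stands only in part: the protocol does not leave the model open, because it lists the fixed effects and the change contrast. The Table 2 covariates do not fill the gap, since they include neither baseline PHQ-9 nor the stratum.

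A reader might also infer three stronger things that the documents do not support.

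- *That leaving out the stratum makes the stated model's standard errors too wide, or adds 3% to 5% to them.* A stratum effect that is constant over time cancels from a change contrast, so under the stated model the omission changes nothing. Some gain would arise there only if the effect varied over time and the model allowed for that.
- *That the PHQ-9 entry window makes change scores especially inefficient.* It tends to do the opposite. Selection on baseline lowers the correlation, but under a linear relation it leaves the slope and residual variance alone and shrinks the baseline variance. Starting from ρ = 0.5 and equal SDs, the ratio of change-score to adjusted variance is 1/0.75 = 1.33. With baseline SD 0.8 it is (0.25 × 0.64 + 0.75)/0.75 = 1.21, and with 0.6 it is (0.25 × 0.36 + 0.75)/0.75 = 1.12.
- *That the allocation is unblocked.* The protocol names a random number generator and stratification ("stratified by levels of drinking to ensure group exchangeability") and is silent on blocks. Such a generator can produce permuted blocks, so silence does not show simple draws.

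**Conclusion.** The point holds as a loss of efficiency. The specified model compares change scores with a free baseline mean in each arm, and handling baseline would be at least as precise in every case.

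The size is uncertain because it rests on an assumed correlation and assumed SDs. The 8% to 19% reduction in standard error belongs to equal SDs and is the favourable end. With a baseline SD 0.8 of the follow-up SD it is 1% to 11%, and with 0.6 it is 1% to 5%. Nearly all of it comes from the baseline. The case for the stratum term is mainly that the analysis should follow the randomisation.

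The change is worth making because it uses only data already collected. Fixing it in advance also removes a later choice between adjusted and unadjusted results.

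**What to change.** Restate the Aim 1 model in the protocol, for example: PHQ-9 at all four visits as the outcome, visit as a category, one baseline mean common to both arms, condition-by-visit terms at the three follow-up visits only, and the drinking stratum used in randomisation as a fixed effect. An acceptable alternative models the follow-up visits with baseline PHQ-9 as a covariate, again with the stratum. Use the same form for the secondary outcomes that are measured at baseline.

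The cost is about one sentence of analysis text and a few degrees of freedom at most. No new data, visits or fathers are needed.

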## TIMEFRAME

In Years 1-4, I will conduct the pilot evaluating LEAD compared to a waitlist control (WL; Aims 1-3). Data analysis (Years 3-4) will explore changes in father MH and secondary outcomes (e.g., child MH) between groups (**Aim 1**). I will use mixed methods to explore mechanisms impacting father, family, and child outcomes (**Aim 2**). In Year 4, I will evaluate feasibility and acceptability of implementing LEAD (**Aim 3**) and develop an R01 proposal. In Year 5, I will complete analysis and manuscripts, disseminate findings in the US and Kenya, and submit the R01 proposal.

| Timeline                                                                                                                                                                                                                                                                                                                                                                                                                                                                                    | Year 1 |   |   |   | Year 2 |   |   |   | Year 3 |   |   |   | Year 4 |   |   |   | Year 5 |   |   |   |
|---------------------------------------------------------------------------------------------------------------------------------------------------------------------------------------------------------------------------------------------------------------------------------------------------------------------------------------------------------------------------------------------------------------------------------------------------------------------------------------------|--------|---|---|---|--------|---|---|---|--------|---|---|---|--------|---|---|---|--------|---|---|---|
| Quarter                                                                                                                                                                                                                                                                                                                                                                                                                                                                                     | 1      | 2 | 3 | 4 | 1      | 2 | 3 | 4 | 1      | 2 | 3 | 4 | 1      | 2 | 3 | 4 | 1      | 2 | 3 | 4 |
| STUDY: Conduct a pilot randomized trial of Learn, Engage, Act, Dedicate (LEAD), a behavioral activation treatment, compared to a waitlist control to: Aim 1. Explore the preliminary effectiveness of LEAD; Aim 2. Use mixed methods to explore mechanisms driving change/no change in father MH, father parenting, and child MH; Aim 3. Explore feasibility and acceptability of implementing task-shifted MH treatment for fathers in a low-resource setting. |        |   |   |   |        |   |   |   |        |   |   |   |        |   |   |   |        |   |   |   |
| Initiate Community Meetings                                                                                                                                                                                                                                                                                                                                                                                                                                                                 |        |   |   |   |        |   |   |   |        |   |   |   |        |   |   |   |        |   |   |   |
| IRB Approvals                                                                                                                                                                                                                                                                                                                                                                                                                                                                               |        |   |   |   |        |   |   |   |        |   |   |   |        |   |   |   |        |   |   |   |
| Hire, Train RAs (ethics; project goals, methods)                                                                                                                                                                                                                                                                                                                                                                                                                                            |        |   |   |   |        |   |   |   |        |   |   |   |        |   |   |   |        |   |   |   |
| Train Enumerators (Assessments) & CHWs (Recruitment)                                                                                                                                                                                                                                                                                                                                                                                                                                        |        |   |   |   |        |   |   |   |        |   |   |   |        |   |   |   |        |   |   |   |
| Supervisor Recruitment/Hiring                                                                                                                                                                                                                                                                                                                                                                                                                                                               |        |   |   |   |        |   |   |   |        |   |   |   |        |   |   |   |        |   |   |   |
| Supervisor Training                                                                                                                                                                                                                                                                                                                                                                                                                                                                         |        |   |   |   |        |   |   |   |        |   |   |   |        |   |   |   |        |   |   |   |
| Counselor Recruitment                                                                                                                                                                                                                                                                                                                                                                                                                                                                       |        |   |   |   |        |   |   |   |        |   |   |   |        |   |   |   |        |   |   |   |
| Counselor Training                                                                                                                                                                                                                                                                                                                                                                                                                                                                          |        |   |   |   |        |   |   |   |        |   |   |   |        |   |   |   |        |   |   |   |
| Participant Recruitment                                                                                                                                                                                                                                                                                                                                                                                                                                                                     |        |   |   |   |        |   |   |   |        |   |   |   |        |   |   |   |        |   |   |   |
| Counselor Refresher Training (2 days)                                                                                                                                                                                                                                                                                                                                                                                                                                                       |        |   |   |   |        |   |   |   |        |   |   |   |        |   |   |   |        |   |   |   |
| Conduct Pilot (Assessment, Treatment/TAU)                                                                                                                                                                                                                                                                                                                                                                                                                                                   |        |   |   |   |        |   |   |   |        |   |   |   |        |   |   |   |        |   |   |   |
| Aim 1 Data Analysis (Explore Clinical Change)                                                                                                                                                                                                                                                                                                                                                                                                                                               |        |   |   |   |        |   |   |   |        |   |   |   |        |   |   |   |        |   |   |   |
| Aim 2 Data Analysis (Mixed-Methods)                                                                                                                                                                                                                                                                                                                                                                                                                                                         |        |   |   |   |        |   |   |   |        |   |   |   |        |   |   |   |        |   |   |   |
| Aim 3 Data Analysis (Implementation Exploration)                                                                                                                                                                                                                                                                                                                                                                                                                                            |        |   |   |   |        |   |   |   |        |   |   |   |        |   |   |   |        |   |   |   |
| Community Dissemination                                                                                                                                                                                                                                                                                                                                                                                                                                                                     |        |   |   |   |        |   |   |   |        |   |   |   |        |   |   |   |        |   |   |   |
| R01 Development; Publish                                                                                                                                                                                                                                                                                                                                                                                                                                                                    |        |   |   |   |        |   |   |   |        |   |   |   |        |   |   |   |        |   |   |   |

